### Plans for collection, laboratory evaluation and storage of biological specimens for genetic or molecular analysis in this trial/future use {33}

Saliva samples are collected in Oragene collection kits (DNA Genotek™, Ottawa, ON, Canada). DNA will be extracted—the primary variant of interest is the Arg16Gly single nucleotide polymorphism of the gene coding for the Beta 2 adrenoreceptor.

## Statistical methods

### Statistical methods for primary and secondary outcomes {20a}

#### Efficacy analysis

Main analyses will be based on the Intention-to-Treat (ITT) principle. The primary outcome will be analysed using a negative binomial regression model that includes time in the study as the exposure (allowing inclusion of data from participants without complete follow-up data) with adjustment for age, sex, socioeconomic status, asthma severity (as evidenced by BTS treatment step) and centre (random effect). Secondary outcomes will be analysed in a similar manner using generalised linear models and the appropriate link function. Comparison of PAQLQ at the final assessment (12 months) between treatment groups will be assessed using analysis of covariance, adjusting for the covariates listed above and baseline PAQLQ. The influence of any missing data on the robustness of the findings will be examined using sensitivity analyses incorporating multiple imputation or other relevant strategies under alternative assumptions.

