### Intervention description {11a}

The intervention groups are as follows:Intervention: treatment guided by spirometry plus asthma control (symptoms)Standard care: treatment guided by asthma control (symptoms)

In the intervention arm, treatment is guided by asthma control, adherence to preventer treatment, recent asthma attacks, recent increase in treatment, short-acting beta-2 agonists (SABA) use, current treatment (ICS dose) plus spirometry (FEV_1_).

In the standard care arm, treatment uses the same factors but does not include spirometry (FEV_1_).

These data, shown in Table 1, are entered into the algorithm which is embedded into the study website and a treatment recommendation is made. This recommendation will be reviewed by the local clinical team who will determine the final treatment.

**Table 1 Tab1:** Data applied each visit for algorithm in intervention and standard care arms

	**Intervention**		**Standard care**	
	**Baseline**	**Follow-up** **(3, 6, 9, 12 months)**	**Baseline**	**Follow-up** **(3, 6, 9, 12 months))**
Asthma Control (ACT/CACT; three categories)	✓	✓	✓	✓
Adherence (at baseline from parent report, at follow-up using electronic logging device if available)	✓	✓	✓	✓
Asthma attack in last 3 months (at baseline in last 6 months)	✓	✓	✓	✓
Step up in treatment since last study visit (at baseline in last 3 months)	✓	✓	✓	✓
SABA use	✓	✓	✓	✓
Current treatment (ICS dose)	✓	✓	✓	✓
FEV_1_	✓	✓		

The algorithm uses web-based software to apply a decision tree which is described in Additional File 1 and the treatment step table in accordance with national guidelines [9] shown in Additional File 2. Based on the factors shown in Table 1, the algorithm makes a recommendation as to whether there should be a step up or step down to a specified treatment or there should be no change to treatment. In some scenarios, e.g., if a child is already on the highest level of treatment, is consistently poorly adherent, or is on a treatment which is not specified in the treatment step table (Additional File 2) then the algorithm will suggest referral for a clinical opinion (RCO). The treatment step table (Additional File 2) then recommends what preventor medication the participant would step up or step down to for the next 3 months. The local clinical team and family will review the treatment recommendation and decide on the final treatment.

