### Sample size {14}

The total sample size is 550. With 275 children in each arm, we will have 90% power (with 5% significance, 2-sided) to detect a 28% reduced risk for asthma attacks from 50% for participants in the control arm to 36% for the intervention arm, allowing for 5% of participants having incomplete primary outcome data.

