## Data collection and management

### Plans for assessment and collection of outcomes {18a}

Data are collected by Local clinical teams at face-to-face appointments with participants. When a face-to-face visit is not possible, data will be collected via telephone appointment or postal questionnaire. Data is recorded on the study website via electronic case report forms and participant questionnaires at baseline and at 3, 6, 9 and 12 months (Table 2).

**Table 2 Tab2:** Timing of outcome measures

	**Baseline assessment**	**Three-month assessment**	**Six-month assessment**	**Nine-month assessment**	**Twelve-month assessment**
Baseline characteristics, including recent asthma history	✓				
Spirometry	✓	✓	✓	✓	✓
Height	✓	✓	✓	✓	✓
Weight	✓				
Asthma Control Test	✓	✓	✓	✓	✓
Paediatric Asthma Quality of Life Questionnaire	✓				✓
Primary outcome (asthma attack)		✓	✓	✓	✓
Adherence to ICS treatment (from electronic logging device)		✓	✓	✓	✓
Exhaled nitric oxide (FeNO)	✓	✓	✓	✓	✓

Spirometry will be measured by staff with an Association of Respiratory Technology and Physiology (ARTP) qualification, or who have received in-house training or undertaken this as part of their routine NHS role. Spirometry will be standardised according to the Global Lung Initiative [23]. A clinically significant reduction in spirometry will be defined as FEV_1_/FVC below the lower limit of normal at the baseline assessment. At the following assessments, as a change of ± 1.6 in change score [24, 25] from the previous assessment.

The ACT [26] (for those aged 12 years and over) and CACT (for younger children) are validated questionnaires used in routine clinical practice to objectively determine asthma control. We will categorise the ACT or CACT score into the three “control states” (fully controlled, partly controlled or uncontrolled.) We will use the validated PAQLQ [27] to measure asthma quality of life at baseline and 12 months post randomisation.

We will measure FeNO in accordance with the standard methodology [28] using the NIOX Vero ® device (Circassia, Oxford, UK). The FeNO measurements will not contribute to the algorithm but are key to the mechanistic aspect of the study.

Participants can opt into providing a saliva sample for the mechanistic component of the trial. A sample can be collected at any trial visit via Oragene self-collection kits (DNA Genotek™, Ottawa, ON, Canada).

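### Only PAQLQ is given its own baseline value as a covariate; the asthma control and ICS dose models, as written, are not, and the primary model has no measure of prior attacks

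*Protocol article*

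**What the plan says.** Under Efficacy analysis, the protocol article states: "The primary outcome will be analysed using a negative binomial regression model that includes time in the study as the exposure", "with adjustment for age, sex, socioeconomic status, asthma severity (as evidenced by BTS treatment step) and centre (random effect". No measure of past attacks is on that list. For the rest it says: "Secondary outcomes will be analysed in a similar manner using generalised linear models and the appropriate link function". PAQLQ is then treated separately, by analysis of covariance with the same covariates plus its baseline value. No other outcome has its baseline named.

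The relevant data are recorded before randomised treatment starts:

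- Table 1 (Intervention description) lists, at baseline in both arms, asthma control by ACT/CACT, current ICS dose, and "Asthma attack in last 3 months (at baseline in last 6 months".
- Table 2 (Plans for assessment and collection of outcomes) lists ACT at baseline and all four follow-up visits, and, at baseline, "Baseline characteristics, including recent asthma history". It does not say whether that history includes a count of attacks.

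The Eligibility criteria require a steroid-treated attack in the previous 12 months. Under Sequence generation, the minimisation factors are centre, age, sex and BTS/SIGN treatment step. The Mediational analysis section ends by leaving full specification to a SAP, which is not shown.

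**The concern.** A baseline measurement of the outcome is usually among its best predictors. The article treats it as an addition to the general list and makes that addition for PAQLQ alone, with no reason for handling asthma control and ICS dose differently. The gap is clearest for asthma control, because nothing on the general list measures how well controlled the child was at entry.

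The primary outcome is a count of attacks, and prior attacks are its natural baseline counterpart. The trial itself uses recent attacks to guide treatment in both arms. The covariate list is also not confined to the minimisation factors, since socioeconomic status was added; attack history was not.

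Neither attack history nor ACT/CACT is a minimisation factor. A chance difference between arms in either would therefore stay in the estimate, and intervals would be somewhat wider than the collected data allow.

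**Working it through.** **The plan's own figure.** The sample size section plans 550 children in two equal arms at 90% power and a two-sided 5% level. Its target is "to detect a 28% reduced risk for asthma attacks from 50% for participants in the control arm to 36% for the intervention arm". It also assumes that 5% will lack a complete primary outcome. With pooled variance and no continuity correction:

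n per arm = [1.96·√(2·0.43·0.57) + 1.2816·√(0.50·0.50 + 0.36·0.64)]² / 0.14² = 260.7, so 261.

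261 / 0.95 = 274.7, so 275 per arm and 550 in total. The figure reproduces (power 0.901 with 261.25 evaluable per arm). It takes no credit for covariates, so nothing below undermines it.

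**Secondary outcomes analysed as continuous.** Adjusting for baseline multiplies the variance by 1 − r², where r is the baseline-to-outcome correlation left after the covariates already in the model. The article gives no r, so these values are assumed:

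| r | Variance factor | SE factor | 550 children carry the information of |
|---|---|---|---|
| 0.2 | 0.96 | 0.980 | 573 |
| 0.3 | 0.91 | 0.954 | 604 |
| 0.5 | 0.75 | 0.866 | 733 |
| 0.7 | 0.51 | 0.714 | 1078 |

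For ICS dose, BTS treatment step is already in the model and overlaps with dose, so the lower rows may be the relevant ones. If asthma control is analysed in its three categories, the formula does not carry over directly.

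**Primary outcome, simulation.** All inputs beyond the planned risks are assumed: 261 per arm; gamma-distributed risk between children with dispersion k of 0.5, 1.0 or 1.5; a share of 0.3, 0.6 or 0.99 of that risk stable from the prior year to follow-up; a prior-year mean of 0.8 attacks before selection; only children with at least one prior-year attack kept; and chances of any attack set to 0.50 and 0.36. There were 250 runs per scenario. Models held treatment arm alone, or arm plus attack history.

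- Adding any attack in the last 6 months: SE ratio 0.993 to 1.000.
- Adding the log of the 12-month count: SE ratio 0.940 to 0.998.
- Power was already 0.964 or more and moved by at most about 1 percentage point.
- Mean log rate ratios with and without attack history agreed to within 0.005, so there was no sign of bias.

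Eligibility explains why the gain is small. A 12-month yes/no history is the same for every child, and the 6-month item separates children only weakly.

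**Primary outcome, analytic check.** Var(log RR) = (1/μ₀ + 1/μ₁ + 2k)/n, with n = 261. For k = 1, a 50% chance of any attack gives μ₀ = 1/0.50 − 1 = 1.0, and 36% gives μ₁ = 1/0.64 − 1 = 0.5625.

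- SE = √((1 + 1.778 + 2)/261) = 0.135; |ln 0.5625| / 0.135 = 4.25; power about 99%.
- If attack history removed 30% of k: SE = √((1 + 1.778 + 1.4)/261) = 0.1265; power 99.5%.

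Over k from 0.25 to 2, with 10% to 30% of k explained, the SE ratio in the planned scenario is 0.895 to 0.994. The 10% to 30% is assumed. The simulation suggests that the documented 6-month item achieves far less.

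**The case against.** The strongest objection is that the article does not exclude the baselines. It is silent for every secondary outcome except PAQLQ, and outcome-specific covariates are the kind of detail a SAP supplies. That stands as a limit: a reader might infer that the plan has decided to leave out baseline ACT/CACT and ICS dose, but the text supports only the weaker statement that they are not named where PAQLQ's is. What survives is the unequal treatment within one paragraph. The primary list is different, since it is set out in full without attack history.

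The list can also be defended as the minimisation factors plus socioeconomic status, which is a standard choice. A reader might infer that precision is given up for no reason, or that the rate ratio is biased. Neither is supported. Under randomisation, leaving out a prognostic covariate does not bias a rate ratio on the log scale, and the simulation agrees.

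A reader might further infer a substantial power gain. With a control rate of 1.0, a rate ratio of 0.72 and k = 1, power is 72%; cutting k to 0.7 or 0.5 raises it to 78% or 82%. This does not hold up. Nothing in the article supports attack history explaining 30% to 50% of the overdispersion. The scenario also moves the 28% reduction from the risk to the rate: a mean of 0.72 gives a 1 − 1/1.72 = 42% chance of any attack, not the planned 36%. On the planned scenario, power at k = 1 is already about 99%.

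Finally, BTS step partly stands in for ICS dose, and the article does not show that a 12-month count is kept. Both points stand and are reflected in the sizes given.

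**Conclusion.** The point holds as an inexpensive improvement in efficiency, not as an error that threatens the trial. It is firmest for asthma control, where no covariate on the list captures the baseline state. It is weaker for ICS dose, because of BTS step, and smallest for the primary outcome.

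For a continuous secondary outcome the SE falls by about 2% at a residual correlation of 0.2 and 13% at 0.5. For the primary outcome it falls by 0 to 0.7% with the 6-month item and 0.2 to 6% with a 12-month count. All these sizes rest on assumed correlations, dispersion and stability of risk. The simulation compared attack history with no other covariates, so any overlap with those already on the list could reduce the gain further. The absence of attack history from the primary list can be read directly; the absence of the ACT/CACT and ICS dose baselines is the natural reading but remains an inference.

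**What to change.** Before unblinding, state in the SAP, and in the protocol if it is amended, that:

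- the asthma control model includes the baseline ACT/CACT score, or the baseline control category if the outcome is analysed in categories;
- the ICS dose model includes baseline ICS dose, alongside BTS step;
- the primary model includes prior attack history: the number of steroid-treated attacks in the 12 months before entry if recorded, otherwise any attack in the last 6 months.

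The first two bring these outcomes into line with PAQLQ. If the SAP already says this, only the published description needs aligning. The change needs wording only and no new data: baseline ACT/CACT, ICS dose and the 6-month attack item are in the tables. Whether the recorded asthma history contains a 12-month count has to be checked first. The Discussion puts the end of follow-up in 2026, so the choice can probably still be fixed in advance; covariates added after results are seen would be open to challenge.

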#### Mediational analysis

Over the 12-month period we will collect the mechanistic outcomes (FEV_1_, FVC and FeNO) at baseline and then every 3 months. We will use causal mediation analysis to explore the indirect effects of treatment mediated by increases in spirometry as measured by FEV_1_, FVC or a reduction in eosinophilic airway inflammation as evidenced by FeNO. We will explore any mechanistic relationship by using time‐to‐first‐asthma‐attack as an outcome in a survival analysis and accounting for repeatedly measured FEV_1_, FVC and FeNO, which is most likely subject to time‐varying confounding, using the methods outlined in Vansteelandt et al. [29]*.*

Safety and other data will be adjudicated at least annually by our oversight committees. Analysis will be fully specified in a Statistical Analysis Plan.

### Interim analyses {21b}

There are no planned interim analyses.

### Methods for additional analyses (e.g. subgroup analyses) {20b}

We plan the following sub-group analyses: age, sex, socioeconomic status, asthma severity.

### Methods in analysis to handle protocol non-adherence and any statistical methods to handle missing data {20c}

Per-protocol analysis and, if appropriate, a complier-adjusted causal estimation (CACE) will be explored to evaluate the influence of compliance on the treatment effect for the primary outcome. Multiple imputation and imputing a range of values for missing data under missing not at random assumptions will be used to explore the robustness of treatment effect estimates.

### Plans to give access to the full protocol, participant level-data and statistical code {31c}

The full protocol is publicly available on NIHR funding and awards website [30]^.^ Non-identifiable participant-level data may be available on request to the Chief Investigator (CI), [name] ([contact]).

## Oversight and monitoring

### Composition of the coordinating centre and trial steering committee {5d}

The core trial team based in the coordinating centre (CI, trial manager, data coordinator, programmer) meets weekly. A Project Management Group (PMG) and Trial Steering Committee (TSC) oversee the project. The PMG meets every 3 months and comprises the CI, grant holders (including clinical, methodological and statistical expertise) and the core trial team. The TSC meets every 12 months and comprises an independent chair, independent clinical and methodological expertise, PPI representation and the CI.

### Composition of the data monitoring committee, its role and reporting structure {21a}

The Data Monitoring Committee (DMC) meets approximately every 12 months. The DMC comprises an independent chair and independent members with clinical and methodological expertise. The DMC reports to the chair of the TSC.

### Adverse event reporting and harms {22}

Within SPIROMAC only adverse events (AEs) and serious adverse events (SAEs) relating to use of spirometry equipment, the NIOX VERO or other study assessments are recorded. An asthma exacerbation is an outcome for this study and is not an AE or SAE. Hospitalisations for planned treatments, elective or emergency treatment will not be considered as an AE or SAE.

Research staff within centres collect data on occurrence of AEs and SAEs at each study visit. Serious related and unexpected AEs are reported to the REC within 15 days of CI becoming aware. All related SAEs will be summarised and reported to the Ethics Committee, the Funder and the Trial Steering Committee in their regular progress reports.

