**Methods:**

This is a multi-centre, randomised controlled trial. Children aged 6–15 years, who have a diagnosis of asthma and have had an exacerbation requiring oral or intravenous corticosteroids in the previous 12 months, will be eligible. Exclusion criteria include being unable to provide spirometry measurement at baseline assessment, having another chronic respiratory condition and being currently treated with maintenance oral steroids or biologicals. Participants will be recruited in both primary and secondary care settings and will be randomised to either receive asthma treatment guided by spirometry plus symptoms (intervention group) or asthma treatment guided by symptoms only (standard care group). Within the spirometry group, treatment recommendations will be dependent on changes in spirometry measurements. Participants will attend assessments 3, 6, 9 and 12 months post-randomisation, where treatment recommendations will be made. The primary outcome is the number of asthma attacks per participant requiring treatment with 1–7 days of oral or intravenous corticosteroid over 12 months, as recorded by the participant or parent. Secondary outcomes include time to first attack, any asthma attack, adverse events, dose of inhaled corticosteroids, asthma control and quality of life. Adherence to inhaled corticosteroid treatment is measured by an electronic logging device.

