### Objectives {7}

The overarching aim of the trial is to compare treatment guided by spirometry plus symptoms against treatment guided by symptoms alone (standard care) in children with asthma who are at risk of an asthma attack. There are efficacy and mechanism aims:(i)Efficacy: To determine the efficacy of treatment guided by spirometry plus symptoms compared to treatment guided by symptoms alone in children with respect to: asthma attacks up to 12 months post randomisation; and asthma control (symptoms); health-related quality of life; adverse events and dose of inhaled corticosteroids.(ii)Mechanism: To determine whether treatment guided by spirometry plus symptoms (compared to treatment guided by symptoms only) leads to improved air flow (FEV_1_), lung volume (FVC) and reduced eosinophilic airway inflammation (fractional exhaled nitric oxide, FeNO) and this physiological change is associated with reduced attacks.

We hypothesise that asthma treatment guided by spirometry will improve expiratory flows and volumes and reduce FeNO, and that this will lead to reduced asthma attacks. SPIROMAC will therefore determine whether the spirometry-guided treatment reduces attacks by achieving one or more of the following physiological changes:Increased airway flow (FEV_1_)Increased lung volume (forced vital capacity, FVC)Reduced eosinophilic airway inflammation, as evidenced by FeNO [19].

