## Assignment of interventions: blinding

### Who will be blinded {17a}

All research and clinical staff at recruiting centres, the participants and their families will be blinded to the randomisation allocation.

Spirometry data will be collected from the participants in both arms and entered into the study website. In participants randomised to the intervention arm, the web-based algorithm considers the spirometry results in the treatment recommendations. In participants randomised to the control arm, the algorithm will not consider the spirometry results.

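### Adverse events are a between-arm outcome, but only those tied to study assessments are recorded, so this outcome cannot show adverse effects of the changed preventer treatment

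*Protocol article*

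**What the plan says.** All references are to the protocol article.

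- **Adverse events as a comparison between arms.** The efficacy aim in Objectives {7} compares the strategies on attacks and asthma control, and then on "health-related quality of life; adverse events and dose of inhaled corticosteroids". The Abstract agrees: "Secondary outcomes include time to first attack, any asthma attack, adverse events, dose of inhaled corticosteroids, asthma control and quality of life". The list under Secondary outcomes also includes adverse events.
- **Analysis.** Under Efficacy analysis, "Secondary outcomes will be analysed in a similar manner using generalised linear models and the appropriate link function". No exception is made for adverse events.
- **What is recorded.** Section {22} states that "only adverse events (AEs) and serious adverse events (SAEs) relating to use of spirometry equipment, the NIOX VERO or other study assessments are recorded". Staff collect these events at each study visit.
- **What is excluded.** The same section says "An asthma exacerbation is an outcome for this study and is not an AE or SAE", and then "Hospitalisations for planned treatments, elective or emergency treatment will not be considered as an AE or SAE".
- **What the arms share.** Section {17a} says "Spirometry data will be collected from the participants in both arms and entered into the study website". Table 2 gives one schedule for all participants, including spirometry and FeNO at baseline and at 3, 6, 9 and 12 months.
- **What differs.** Under Intervention description {11a}, both arms use the same inputs to the treatment algorithm, except that FEV1 is used only in the intervention arm. The output is a step up, a step down, no change, or referral for a clinical opinion.

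**The concern.** An outcome that compares two randomised strategies should be able to respond to what was randomised. Here the recorded events come from procedures that every child undergoes in the same way. The events that the randomised contrast could change, namely adverse effects of a different preventer treatment, are not recorded under the stated rule.

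The risk lies in interpretation. A table showing no difference in adverse events would be read as reassurance about the treatment strategy in children aged 6–15, in a trial whose Discussion expects relevance to national and international guidelines. The data behind that table would carry no information on the question.

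The hospitalisation sentence in {22} adds a smaller difficulty. Read plainly, it removes emergency admissions from adverse-event status without qualification. That would include an emergency admission following a study spirometry test, which the opening sentence of the section appears to include.

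**Working it through.** **1. The plan's own figure.** The article gives no rate or power for adverse events. Its only figure is the sample size: 50% versus 36%, two-sided 5%, 90% power, 5% incomplete data, 275 per arm. With pooled variance and no continuity correction:

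n = [z(0.975)·√(2p̄(1−p̄)) + z(0.90)·√(p1(1−p1) + p2(1−p2))]² / (p1−p2)²

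With p1 = 0.50, p2 = 0.36, p̄ = 0.43:

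n = [1.960·√0.4902 + 1.282·√0.4804]² / 0.14² = 260.7, so 261 per arm.

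261/0.95 = 274.7, so 275 per arm and 550 in total. The stated size reproduces, and 261 evaluable per arm (95% of 275, rounded down) is used below.

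**2. Who can contribute a recorded event.**

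| Source of event | Recorded under {22}? | Can differ by arm by design? |
|---|---|---|
| Spirometry, FeNO device, other study assessments | Yes | No: same assessments and schedule |
| Adverse effect of a preventer treatment change | No | Yes: this is the randomised contrast |
| Asthma exacerbation | No, but captured as an efficacy outcome | Yes |

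No row is both recorded as an adverse event and able to differ by design.

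**3. Consequence.** Let a be the probability of an assessment-related event, and let t1 and t0 be the probabilities of a treatment-related event in the intervention and standard care arms. The recorded rates are a in both arms, so the expected difference is a − a = 0 for every t1 and t0. A 5% two-sided test then rejects with probability of at most about 5%, however large t1 − t0 is.

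**4. What recording would allow.** The article gives no rates, so the following are assumed only to show a range. With 261 evaluable per arm, two-sided 5%:

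power = Φ{[√n·|p1−p2| − 1.960·√(2p̄(1−p̄))] / √(p1(1−p1) + p2(1−p2))}

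| Assumed treatment-related event rates | Power if recorded in both arms | Rejection probability as now recorded |
|---|---|---|
| 2% vs 4% | 27% | about 5% |
| 5% vs 10% | 58% | about 5% |
| 10% vs 15% | 41% | about 5% |
| 20% vs 30% | 75% | about 5% |
| 10% vs 20% | 89.5% | about 5% |

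Example, 5% vs 10%: √261 = 16.16; numerator 16.16·0.05 − 1.960·√0.13875 = 0.808 − 0.730 = 0.078; denominator √0.1375 = 0.371; Φ(0.21) = 0.58.

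Even with full recording, power would be modest for uncommon events. Recording would still give an estimate with a confidence interval for the right quantity.

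**The case against.** A reader might infer that the trial cannot detect harm from spirometry-guided treatment at all. The documents do not support that. The arms are also compared on number of attacks, any attack, time to first attack, asthma control, the quality-of-life questionnaire and ICS dose. Harm through more attacks or worse control, for example after a step down, would show there. Greater steroid exposure would show in ICS dose, although that is exposure and not an adverse effect.

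Other parts of the defence also stand:

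- Taking exacerbations out of adverse-event status loses nothing important. Corticosteroid-treated attacks are the primary outcome, with retrieval from medical records for those lost to follow-up.
- It should not be inferred that the data monitoring committee would see no safety signal by arm. The article does not say what the committee sees, and it refers to review of safety and other data.
- Nothing says that the intervention will increase treatment overall; the algorithm can step in either direction.
- Recording only research-procedure events may be deliberate, since the treatment steps follow national guidelines and local clinicians decide the final treatment.
- The absence of a height outcome is not an error. Height appears in Table 2 ("Timing of outcome measures") and may serve only to standardise spirometry.

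The last line of defence is that the article condenses a fuller protocol and leaves analysis to a statistical analysis plan. That does not answer this point. Section {22} states a restriction with the word only, so nothing was merely left out, and no analysis plan can recover events that were never recorded. A deliberate narrow scope explains the recording rule; it does not justify listing the result as a comparison of the two strategies.

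**Conclusion.** The point holds for the adverse-event outcome. Objectives {7} and the secondary outcome list promise a comparison that the recording rule in {22} cannot deliver. The expected between-arm difference is about zero whatever the effect of the changed preventer treatment, so the outcome has no power against treatment-related adverse effects beyond the roughly 5% false-positive rate.

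This rests on two assumptions: that attendance at assessments does not differ materially between arms, and that the treatment itself does not noticeably change how children tolerate the tests. Either could produce a small difference, but not one that measures treatment side effects.

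The defect concerns one secondary outcome and its interpretation. It does not affect the primary analysis or the sample size, and the trial keeps other outcomes that can show some forms of harm.

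**What to change.** **Minimum, needing no new data.** Reconcile Objectives {7}, the Abstract and the secondary outcome list with {22}. Relabel the outcome as adverse events related to study assessments, remove it from the between-arm efficacy objective, report it descriptively, and state that it is not evidence on the safety of spirometry-guided treatment. This can be done at any time before reporting in 2027.

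**Where follow-up remains.** Extend the recording rule to adverse events and serious adverse events possibly related to asthma preventer treatment, collected identically in both arms at the existing visits. Section {25} requires permission from the funder, sponsor, management and steering groups, ethics committee and NHS offices, and the new item would have to reach all sites (32 were already recruited in the pilot). Recruitment began in January 2023 and follow-up ends in 2026, so data will be missing or incomplete for children already followed up. The report should state the period covered.

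**Hospitalisation sentence.** Clarify it so that an emergency admission related to a recorded event category is not excluded. Deleting the reference to emergency treatment would not by itself make unrelated admissions recordable, because the opening sentence of {22} would still limit what is captured.

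**Optional.** Report change in age- and sex-standardised height from baseline to 12 months by arm, adjusted for baseline height, as an exploratory safety analysis beside ICS dose. Height is already measured at all five visits, so the cost is one extra analysis of covariance.

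### The harms section says procedure-related SAEs are recorded and reported, yet denies AE or SAE status to emergency hospitalisation with no exception for an admission caused by a study procedure

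*Protocol article*

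**What the plan says.** Adverse event reporting and harms {22} sets the rules in a few consecutive sentences.

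- Scope: the only AEs and SAEs captured are those "relating to use of spirometry equipment, the NIOX VERO or other study assessments are recorded".
- Asthma attacks: "An asthma exacerbation is an outcome for this study and is not an AE or SAE".
- Hospitalisation: "Hospitalisations for planned treatments, elective or emergency treatment will not be considered as an AE or SAE".
- Expedited reporting: "Serious related and unexpected AEs are reported to the REC within 15 days of CI becoming aware".
- Periodic reporting: "All related SAEs will be summarised and reported to the Ethics Committee, the Funder and the Trial Steering Committee in their regular progress reports".

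Adverse events are also an outcome. The efficacy aim in Objectives {7} ends its list with "health-related quality of life; adverse events and dose of inhaled corticosteroids", and Outcomes {12} names adverse events among the secondary outcomes.

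**The concern.** The first rule brings procedure-related SAEs in. The hospitalisation rule takes every hospitalisation out, emergency ones included, without separating those a study procedure caused from those it did not. A site whose participant is admitted as an emergency after a problem during spirometry cannot follow both sentences: under one the event is a related SAE to be recorded and reported, under the other the admission is neither an AE nor an SAE.

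At stake is whether such an event reaches the reporting routes that the same section sets up, and whether the trial's count of related SAEs can be taken at face value. Because adverse events are a listed outcome, the wording bears on a reported result as well as on site procedure.

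**Working it through.** No arithmetic applies. The check is to ask which emergency admissions the hospitalisation sentence can still act on once the other two sentences have been applied, and then to look elsewhere for an exception.

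| Emergency admission | Scope sentence | Exacerbation sentence | What the hospitalisation sentence adds |
|---|---|---|---|
| Unrelated to any study assessment, not asthma | already out | not needed | nothing |
| Asthma attack unrelated to any study assessment | already out | also out | nothing |
| Related to a study assessment and classed as an asthma exacerbation | in | out | nothing further; already removed, against the scope sentence |
| Related to a study assessment, not an exacerbation | in | does not apply | removes it, against the scope sentence |

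Step 1. The first two rows show that the word *emergency* is not needed to keep out unrelated admissions or ordinary attacks.

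Step 2. The fourth row is the only one in which the hospitalisation sentence changes the result, and there it removes what the scope sentence brings in.

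Step 3. The third row shows the same conflict arising from the exacerbation sentence. If airway narrowing provoked at a study visit is labelled an exacerbation, it leaves the AE and SAE record whether or not the procedure triggered it.

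Step 4. Both reporting sentences depend on an event being serious and related. If the admission is the only reason the event is serious, and admission does not count, neither the 15-day report nor the periodic summary is triggered.

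Step 5. The rest of the article gives no exception. Procedure for unblinding {17b} mentions adverse events only to explain why emergency unblinding is not needed. The closing lines of Mediational analysis say that oversight committees look at safety data at least annually, but not which admissions count.

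**The case against.** The best defence is that the sentence removes hospitalisations and not the events behind them. The scope sentence says related events are recorded, and staff ask about them at each visit, so a collapse during spirometry could still be entered as a related AE. On this view the second and third sentences merely remind sites that attacks and admissions for treatment are not in themselves AEs. That reading is reasonable and may be what was meant. The text does not say so, however, and on that reading the word *emergency* does no work, since unrelated admissions are already out of scope.

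A reader might go further and infer that procedure-related emergencies would never be recorded, or that the 15-day rule is left empty. The documents do not support either. The underlying event can still be recorded as a related AE, and the 15-day rule still covers unexpected related events that are serious for a reason other than admission.

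A reader might also infer that the Data Monitoring Committee is kept from safety data, because the periodic-report sentence does not name it. That does not follow: the list concerns regular progress reports, and Mediational analysis separately sends safety data to the oversight committees at least annually.

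Two more points for the plan stand. Spirometry is done in both arms, so the rule applies equally and gives no evident bias between them. An event classed as an exacerbation and treated with 1–7 days of oral or intravenous corticosteroids still counts in the primary outcome; what is lost is its attribution to the procedure.

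Finally, the full protocol is said to be public and is not shown here. It may be worded differently. But the article states this rule outright, so this is a conflict in what is written and not a detail left to another document.

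**Conclusion.** The point holds as an internal contradiction. The section cannot both record and report procedure-related SAEs and deny AE and SAE status to every emergency hospitalisation. The consequence is limited to events that are related to a study assessment and serious only because of an emergency admission. Those could be missing from the SAE count, the 15-day report to the ethics committee and the periodic summary.

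The size cannot be put in numbers, because the article gives no rate for such events; there may be none. The conclusion rests on two assumptions: that hospitalisation would otherwise be one of the criteria for seriousness (the article does not define the term, though excluding hospitalisation makes little sense if it is not), and that sites apply the sentence as written. Nothing here shows that any event has been left out so far.

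**What to change.** Reword the hospitalisation sentence so that it excludes only admissions that are planned or elective, and those unrelated to study procedures. Add that an unplanned admission related to a study assessment is recorded and reported as a related SAE, including when the event is also classed as an asthma exacerbation; it would then also count as an attack wherever it meets the primary outcome definition.

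Put the same wording in the full protocol and the site guidance on SAEs. If the full protocol already contains the exception, only the article needs correcting. The article expects participant follow-up to finish in 2026, so a correction can still apply to remaining visits.

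The cost is a small text change and a few extra relatedness assessments at sites. The design, sample size and efficacy analysis are unaffected.
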